#### Secondary endpoints

The overall survival analysis will be performed in the ITT population using the same methods.

Tolerance assessments will be conducted throughout treatment and will continue until completion of follow-up using CTCAE-V4.02 criteria. Two periods will be distinguished, events appearing during or within 2 months of the treatment period and late toxicities appearing within 5 years after the end of treatment and which will be considered attributable to radiotherapy. The rate of patients with at least one adverse event will be compared between the two treatment arms.

Quality of life will be evaluated at baseline, at 6 months and then at 1 year and annually until the fifth year of follow-up after treatment using the EQ-5D questionnaire. The quality of life analysis will be carried out on the ITT population. The level of quality of life at inclusion and its evolution during the monitoring period will be compared between the treatment arms. The 10% difference between initial assessment and subsequent assessments of the overall quality of life score will be considered clinically relevant as defined by Osoba et al. [19, 20].

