## Methods and design

### Study design

The ETOILE trial is a multicenter open-label randomized parallel-group superiority trial comparing carbon ion therapy with standard radiotherapy, including a treatment by photons or protons. Patients will be enrolled in French reference centers for cancer treatment. Patients fulfilling the eligibility criteria will be randomized into two arms using a 1:1 ratio (experimental arm: carbon ion therapy; control arm: photon or proton therapy). Follow-up takes place 2 months and 6 months after the end of radiotherapy, then every 6 months during 5 years.

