### Study objectives and endpoints

The primary outcome is the progression-free survival (PFS) defined as the time from randomization to the first relapse or death, whatever the cause, or to the latest news date. Progression is defined according to RECIST v1.1 criteria [17] based on standard medical imaging (CT or MRI), and confirmed 6 months later. An independent committee unaware of the treatment group will validate all progressions.

Secondary outcomes include: the tolerance profile assessed using CTCAE-V4.02 grades; survival without locoregional progression; survival without metastases; overall survival; quality of life using the EQ-5D-3L. Associated health-economic and radiobiological studies are also planned.

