### Randomization

Randomization will be done using an Interactive Web Response Systems (IWRS). Stratification parameters include the center and the type of cancer (adenoid cystic carcinoma versus sarcoma and chordoma). As the trial design is open-label, no blinding of treatment assignment is possible.

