### Statistical analysis

#### Primary endpoint

The primary endpoint will be analyzed on the intention-to-treat (ITT) population comprising all randomized patients in the arm where they were randomized. A per-protocol analysis will also be performed in patients without major deviation from the protocol. The evaluable population for treatment tolerance will be all patients who received at least one session of radiotherapy of any kind. PFS will be calculated from the date of randomization to the date of first evidence of a documented relapse, or until the date of death regardless of cause, or until the date of last news (data from patients who did not present the event at the time of the analysis will be censored). It will be estimated in each arm by the Kaplan-Meier method and compared between the two treatment arms by a Log-Rank test.

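### Late toxicities, unlike early events, are described as those attributable to radiotherapy, which on the natural reading leaves an open-label comparison exposed to arm-dependent attribution

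*Protocol article*

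**What the plan says.** Under Statistical analysis, Secondary endpoints, the protocol article splits tolerance into two periods.

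- **Early period:** "Two periods will be distinguished, events appearing during or within 2 months of the treatment period". No judgement of cause is attached.
- **Late period:** "late toxicities appearing within 5 years after the end of treatment and which will be considered attributable to radiotherapy".
- **Comparison:** "The rate of patients with at least one adverse event will be compared between the two treatment arms". This sentence does not repeat the attribution condition and does not say which period it covers.

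Four statements elsewhere in the article bear on this.

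- Study objectives and endpoints includes among the secondary outcomes "the tolerance profile assessed using CTCAE-V4.02 grades".
- Statistical analysis, Primary endpoint, defines the denominator: "The evaluable population for treatment tolerance will be all patients who received at least one session of radiotherapy of any kind".
- Randomization states: "As the trial design is open-label, no blinding of treatment assignment is possible".
- Study objectives and endpoints provides a safeguard for the primary outcome: "An independent committee unaware of the treatment group will validate all progressions". No similar provision is described for adverse events or their cause.

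**The concern.** The two periods appear to follow different counting rules. An early event counts because it happened. A late event, on the natural reading, counts because it happened and was put down to radiotherapy.

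The second rule rests on opinion. Patients have unresectable, inoperable or macroscopically incompletely resected tumours, so a symptom arising years later may come from the tumour, earlier surgery or the radiation. The arms are easy to tell apart, since carbon ions are given in Pavia and photons or protons in France. Anyone who knows the arm may attribute more readily to the newer beam, or less readily if they favour it.

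Late toxicity is a main part of the benefit-risk comparison. Differential attribution could create a difference between arms or hide a real one. The article describes no all-cause late comparison that would show this happening.

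**Working it through.** The article gives no toxicity rate, attribution rate or power for tolerance, so it has no figure of its own to reproduce. The check has three parts.

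**1. The passages side by side**

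| Element | Early events | Late events | Progression |
|---|---|---|---|
| Causality condition | None | Attributable to radiotherapy | Not applicable |
| Knowledge of arm | Open-label | Open-label | Validated by a committee unaware of arm |

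Of the three, only late toxicity both depends on a judgement of cause and has no blinded assessment described.

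**2. How large the effect could be (illustration)**

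Inputs from the article: 1:1 allocation; 108 patients per arm calculated; 250 in total as the recruitment target, so 125 per arm. These stand in for the number treated.

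Assumed inputs: the true late-event proportion p, equal in both arms, and the attribution probabilities a1 and a2.

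Counted rate in an arm = p × a, so the spurious difference = p × (a1 − a2).

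| p | a1 vs a2 | Counted rates | Spurious difference | Chance of two-sided p<0.05, 108 to 125 per arm |
|---|---|---|---|---|
| 20% | 90% vs 80% | 18% vs 16% | 2 points | about 7% |
| 30% | 90% vs 70% | 27% vs 21% | 6 points | 18% to 20% |
| 50% | 90% vs 70% | 45% vs 35% | 10 points | 32% to 36% |
| 70% | 90% vs 60% | 63% vs 42% | 21 points | 88% to 92% |

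The last row is a deliberately extreme case. With equal attribution, or with all late events counted, the difference is 0 and the chance is the nominal 5%.

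One row worked through, at 125 per arm:

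- pooled rate 24%; standard error under no difference = √(2 × 0.24 × 0.76/125) = 0.0540
- standard error at the counted rates = √(0.27 × 0.73/125 + 0.21 × 0.79/125) = 0.0539
- (1.96 × 0.0540 − 0.06)/0.0539 = 0.85, and P(Z > 0.85) = 0.20.

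**3. Whether stopping the count at progression is a safe alternative**

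Inputs from Sample size calculation: 5-year PFS 70% (carbon) and 50% (control). Assumptions: constant hazards, late events independent of progression, and the same true late-event rate in both arms, 30% at 5 years if nothing stopped the count.

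- late-event hazard = −ln(0.70)/5 = 0.0713 per year
- PFS hazard: carbon −ln(0.70)/5 = 0.0713; control −ln(0.50)/5 = 0.1386
- proportion with a late event before a PFS event = [h_late/(h_late + h_PFS)] × [1 − exp(−5(h_late + h_PFS))]
- carbon: 0.500 × (1 − 0.70 × 0.70) = 0.500 × 0.51 = 25.5%
- control: 0.340 × (1 − 0.70 × 0.50) = 0.340 × 0.65 = 22.1%

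That is 3.4 points against carbon with no true difference. At a 20% late-event rate the figures are 16.9% and 14.6%, or 2.3 points. The arm with better disease control is at risk for longer and so looks more toxic. A cumulative incidence with progression as a competing event estimates these same quantities and shows the same gap.

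A rate per patient-year does not. Mean time at risk to first late event, PFS event or 5 years is 0.51/0.1427 = 3.57 years (carbon) and 0.65/0.2100 = 3.10 years (control). Then 0.255/3.57 and 0.221/3.10 both return 0.071 per year.

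**The case against.** **The article does not name who judges attribution.** A reader might infer that unblinded staff decide. That is plausible, since the trial is open-label and the blinded committee is mentioned only for progressions. It is still an inference: an article condenses the full protocol, which could name a blinded assessor or include all-cause tables. This objection stands, and the point should not be put as established fact.

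**The wording allows a second reading.** The phrase could mean that every late toxicity is deemed radiotherapy-related by convention, and the comparison sentence carries no condition. Attribution bias then disappears, although tumour symptoms would be labelled toxicity and could fall more on the arm that progresses more. The restrictive reading is the more natural one, but the ambiguity is real. It does not follow that the comparison is wrong on either reading. On each, bias is possible but not shown.

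**The criterion is nominally the same in both arms.** Every patient in the tolerance population received radiotherapy, and attribution is to radiotherapy rather than to carbon ions. This is correct: bias needs the judgement to differ by arm. It limits the claim without answering it, because nothing described prevents such a difference.

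**The magnitude is assumed and the endpoint is secondary.** Both are true. On the more modest assumptions, a chance of 7% to 20% against a nominal 5% is a moderate distortion. Tolerance comes first among the secondary outcomes under Study objectives and endpoints, but the abstract puts overall survival and local control ahead of it.

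**Conclusion.** The point holds in a limited form. The article states a rule for late events that it does not apply to early ones. On the natural reading, the late-toxicity comparison in this open-label trial can be affected by arm-dependent attribution, and no safeguard is described.

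The documents do not show that bias will occur, which way it would run or how large it would be. The 2 to 6 points (up to 10 at a 50% event rate, and 21 in the extreme case) rest wholly on assumed event and attribution rates. Nor do they show that unblinded staff make the call.

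This is a worthwhile, inexpensive improvement to a secondary analysis. It does not touch the PFS comparison.

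**What to change.** 1. Record every late event, with attribution to radiotherapy as a separate field and not as a condition for counting it.
2. Compare all late events between arms by CTCAE grade regardless of attribution. Report the attributable-only comparison alongside as supportive, and state who judges attribution and whether they know the arm.
3. Do not cut a simple proportion off at progression. If events after progression or new anticancer treatment are to be excluded, do so in a sensitivity analysis that accounts for time at risk, such as cause-specific hazards or rates per patient-year censored at progression.

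**Cost:** a sentence or two in the analysis section and an extra table, plus the sensitivity analysis if wanted. CTCAE assessment is already planned until the end of follow-up.

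**Downside:** unrelated and tumour-related events enter the all-cause comparison. They add noise, and the arm that progresses more contributes more of them. Neither comparison is free of bias alone, which is why both should be shown.

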### Sample size calculation

The study is calibrated to detect a treatment effect hazard ratio (HR) of 0.515 under the proportional hazards assumption, translating in an absolute improvement of the 5-year PFS rate of 20% in favor of the experimental arm (70% in the experimental arm vs 50% in the control arm).

A total of 92 events [East Software- Copyright@Cytel inc. 1994] notified in the study would have 90% power to show statistically significant PFS at a 2-sided alpha. Considering initial recruitment duration of 24 months and a 5-year follow-up for the last included patient, 108 patients per arm would be randomized in the study. To optimize the study and consider the possibility of withdrawal of consent and patients lost to follow-up, the recruitment objective was set at 250 patients.

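### The only stated toxicity comparison counts patients with any adverse event, with no severity threshold and no stated period, so it does not use the CTCAE grades that define the tolerance endpoint

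*Protocol article*

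**What the plan says.** Under Study objectives and endpoints, the Protocol article lists among the secondary outcomes "the tolerance profile assessed using CTCAE-V4.02 grades". The endpoint is therefore defined by severity.

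Under Statistical analysis, Secondary endpoints, it describes the timing: "Two periods will be distinguished, events appearing during or within 2 months of the treatment period and late toxicities appearing within 5 years". Late toxicities carry a further qualification: "which will be considered attributable to radiotherapy". The comparison follows directly: "The rate of patients with at least one adverse event will be compared between the two treatment arms".

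The analysis set is given under Primary endpoint: "The evaluable population for treatment tolerance will be all patients who received at least one session of radiotherapy of any kind".

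No other between-arm toxicity comparison appears in the article. The comparison sentence names no grade, no seriousness criterion and no period. No expected adverse event rate and no power for toxicity are stated anywhere.

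**The concern.** The endpoint is graded but the stated comparison is not. Each patient is reduced to yes or no for at least one event, so the measure cannot tell an arm with mostly mild events from an arm with many severe ones. The article does not leave this choice to another document; it names the measure.

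Tolerance carries much of the benefit-risk judgement in this trial. The design tests superiority on progression-free survival, and the control arm itself assigns proton therapy by predicted normal tissue complication probability, so differences in toxicity are treated as important. The arms may well differ in how severe the harm is rather than in whether any event occurs. If the main comparison ignores severity, a finding of no difference could be read as equal tolerance when it is not.

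For late events there is a second issue. A simple proportion over 5 years takes no account of how long each patient was alive and assessed. If one arm lives longer, it has more time in which to show a late effect.

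**Working it through.** There is no stated toxicity figure to reproduce. The check has three parts: what the measure can see, how it performs under assumed rates, and what unequal time at risk does to a late-event proportion.

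**Inputs from the article**
- Sample size: "the recruitment objective was set at 250 patients" (Sample size calculation).
- Allocation: "randomized into two arms using a 1:1 ratio" (Study design), so 250 / 2 = 125 per arm. The tolerance set is limited to treated patients, so 125 is an upper figure.
- Two-sided testing. The level is not printed in the article; 5% is assumed.
- All toxicity rates below are assumptions.

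**1. What the measure can see**

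Suppose grade 3 or higher events occur in 25% of one arm and 10% of the other, and the same share of patients in both arms has at least one event of some grade. The quantity compared under the stated measure is then:

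| Any event, both arms | Difference in stated measure | Difference in grade 3 or higher |
|---|---|---|
| 98% | 0 points | 15 points |
| 60% | 0 points | 15 points |

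The severe difference is invisible in both rows. The loss comes from ignoring grade and needs no ceiling. A ceiling makes it more likely, because it leaves the any-event rates little room to differ.

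**2. Power under assumed rates**

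Normal approximation with pooled variance under the null, n = 125 per arm:

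- p̄ = (p1 + p2) / 2
- s0 = √(2 p̄ (1 − p̄) / n)
- s1 = √(p1(1 − p1)/n + p2(1 − p2)/n)
- power = Φ((|p1 − p2| − 1.96 s0) / s1)

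Worked case, any event 98% vs 96%: p̄ = 0.97, s0 = 0.02158, s1 = 0.02154, so (0.02 − 1.96 × 0.02158) / 0.02154 = −1.035 and power = 15%.

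Worked case, grade 3 or higher at 25% vs 10%: p̄ = 0.175, s0 = 0.04806, s1 = 0.04712, so (0.15 − 1.96 × 0.04806) / 0.04712 = 1.18 and power = 88%.

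| Measure | Assumed rates | Power |
|---|---|---|
| Any event, near ceiling | 98% vs 96% | 15% |
| Any event, near ceiling | 99% vs 97% | 20% |
| Any event, near ceiling | 95% vs 90% | 32% |
| Any event, away from ceiling | 50% vs 35% | 67% |
| Any event, away from ceiling | 60% vs 40% | 89% |
| Grade 3 or higher | 20% vs 10% | 60% |
| Grade 3 or higher | 20% vs 8% | 78% |
| Grade 3 or higher | 25% vs 10% | 88% |

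The rows use differences of different size, so the gap between 15% and 88% is not a like-for-like comparison of methods. It shows only that if any-event rates are near the ceiling, the differences still possible are small and hard to detect, while plausible severe-event differences remain within reach of this sample size.

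**3. Time at risk for late events**

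Take the design's 5-year progression-free survival of 50% and 70%, assume exponential times, and suppose, as an upper illustration, that observation for late effects stopped at progression or death.

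- Hazards: −ln(0.50)/5 = 0.1386 and −ln(0.70)/5 = 0.0713 per year.
- Mean observation within 5 years: 0.50/0.1386 = 3.6 years and 0.30/0.0713 = 4.2 years.
- With the same late-event hazard h = 0.06 per year in both arms and λ the hazard above, the 5-year proportion is h/(h + λ) × (1 − exp(−5(h + λ))), which gives 19% (control) and 22% (carbon).

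Identical late-event hazards would thus appear as a 3-point disadvantage for carbon. The article continues toxicity assessment to the end of follow-up, so death rather than progression would usually end observation, and the gap would probably be smaller. The same formula is also the cumulative incidence with a competing event, so cumulative incidence alone does not remove the effect.

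**The case against.** The strongest reply has four parts.

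First, a reader might infer that the comparison saturates near 100% in both arms and would show no difference whatever the severe toxicity. The documents do not support that. They give no adverse event rate, and the words of any grade are not printed; that reading rests on the absence of a threshold. Late events are limited by wording to "late toxicities appearing within 5 years after the end of treatment and which will be considered attributable to radiotherapy". If that acts as a filter (it could also be a blanket assumption), the late rate may be well below the ceiling, where the comparison has reasonable power. This stands, and the point does not depend on saturation.

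Second, the endpoint is a profile by grade, so tabulation by grade is to be expected, and a grade cut-off or competing-risk method is commonly left to a full protocol or analysis plan that is not shown here. This stands in part. Silence on such detail would be no finding. But the article states which measure will be compared, and that measure leaves out the dimension that defines the endpoint. If the full documents set a threshold, the sponsor need only bring the sentence into line.

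Third, a reader might infer that the early and late windows overlap, because the late window is counted from the end of treatment without a start. The article says that two periods are distinguished and calls the second one late, so separate windows are the natural reading. This is loose wording, not an error.

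Fourth, the time-at-risk argument is conditional on a survival difference, and the article does not expressly fix a crude 5-year proportion for late events. That is fair. It supports the choice of method in the fix but is not a fault on its own.

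**Conclusion.** The point holds in a limited form. The one stated between-arm toxicity comparison has no severity threshold and does not say whether it is made per period, so it does not use the grades that define the tolerance endpoint. A difference in severe toxicity can therefore go unseen in it at any event rate.

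How likely that is depends on rates the article does not give. It is most plausible in the early period, if nearly all patients have some event; power is then about 15% to 32% for the small differences still possible. Where rates are away from the ceiling the comparison can detect a difference in frequency, but a result in either direction says nothing about severity.

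The figures rest on 125 treated patients per arm, a two-sided 5% level and assumed rates. This concerns a secondary endpoint, and because grades are collected nothing is lost for good. It should be corrected before the analysis.

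**What to change.** Replace the comparison sentence with one that specifies the following:

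- **Measure:** the proportion of patients with at least one CTCAE grade 3 or higher event, compared between arms.
- **Periods, separately:** early, from the start of radiotherapy to 2 months after its end; late, from then up to 5 years.
- **Late events:** time to first grade 3 or higher event, by cumulative incidence with death as a competing event and censoring at the last toxicity assessment. Add a cause-specific hazard comparison, because cumulative incidence alone does not remove a difference in survival.
- **Attribution:** state whether late events are filtered by judged attribution or all counted as attributable.
- **Any-event rate:** keep it as descriptive, by arm and period.

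The cost is protocol or analysis plan wording and a little more analysis. Grades are already collected, so no new grading is needed, and the sample size does not change.

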#### Interim analysis

An interim analysis is planned for effectiveness or futility. This analysis will be carried out when approximately 50% (46 events) of the final number of PFS events has been reached. The significance level at this interim analysis to establish the superiority or futility of experimental treatment over control with regard to PFS will be determined based on the observed number of events, using the O’Brien & Fleming boundaries as implemented by the Lan-DeMets alpha spending method (Lan and DeMets 1983) in order to control the overall Type I error rate.

Using planned enrollment rate, this analysis should be performed 42 months after first included patient. For example, if the number of events at the time of interim efficacy analysis is exactly 46, the bounds to use during this analysis according to Lan Demets rules will be *p* = 0.0031 and *p* = 0.8443 respectively to reject H0 and H1.

